**Fig. 1 Fig1:**
[figure not shown]
Flow diagram of the study design

**Fig. 2 Fig2:**
[figure not shown]
Comparative analysis of hypertension management strategies

### Study intervention

The study intervention focuses on the development and application of IoT-based hypertension monitoring and management information system. This system integrates intelligent blood pressure monitoring devices and software to dynamically track and manage hypertensive patients in primary care settings. The intervention involves deploying six blood pressure health management all-in-one machines, two electronic display screens, and an intelligent hypertension monitoring information system in the general practice clinics of Liyuan Community Health Center and Xiaogao Community Health Station. These devices are connected to the health hut and the residents’ personal health records, enabling real-time data transmission and analysis. The system utilizes identity information, health insurance cards, and facial recognition to ensure accurate data collection and upload. The primary goal is to monitor blood pressure data, control rates, and standardized management rates. By leveraging IoT and AI technologies, the intervention seeks to enhance the efficiency and quality of hypertension management in primary care (Fig. 3).

The system’s innovative features include interoperability with existing health hut, automated risk assessments, and intelligent decision support. It employs a modular design for scalability, enabling future expansion to additional metrics like blood glucose and weight, while standardized data formats and open interfaces facilitate integration with external platforms such as the Beijing Community Health’s electronic health record (EHR) and Tongzhou District Performance Evaluation Platform. Security is ensured through role-based access control [14]. Key functionalities include real-time data transmission (via ID card, medical insurance card, or facial recognition), dynamic tracking of standardized management and control rates, and dashboard visualization of blood pressure trends for clinicians and patients. During development, rigorous testing was conducted: 500 simulated patient datasets were used to validate system functionality, including seamless data upload to individual health records and public health systems, accurate calculation and display of monthly/quarterly metrics on clinic screens, automated risk alerts for uncontrolled hypertension, and generation of quarterly/annual trend reports. The system successfully passed testing, confirming capabilities in risk alerts, statistical analysis, and user interface usability, and is now operational in the clinical application phase. In the clinical phase, 2000 hypertensive patients are chosen at random from the current management pool to participate in the trial. The intervention group (*n* = 1,000) consists of patients from five family doctor teams in Liyuan Community Health Center and Xiaogao Station equipped with the new system, while the control group (*n* = 1,000) comprises patients from other stations without the system. The intervention group uses the IoT-based system for blood pressure measurements, with data automatically uploaded to health records and displayed on screens.

Patients in the intervention group can view their daily blood pressure conditions on the display. If there are any abnormalities, they can receive timely treatment. They can also print out the results, health education prescriptions, and blood pressure trend charts on-site. Managers can inquire about the number of people taking blood pressure measurements, the standardized management rate and the blood pressure control rate of each team in our hospital on a daily, monthly and quarterly basis. Once a month, the information is summarized, a team meeting is held to analyze the data collected by the system, statistics are analyzed and made public, the team is urged to strengthen the blood pressure management and strive to improve their own level, and the doctors are urged to refer patients affecting the control rate to the higher-level hospitals so as to form a good diagnosis and treatment pattern. The control group is managed in the traditional way. Patients only have their blood pressure measured in the health hut, and the data is not included in the new system for statistics. Management is carried out in accordance with the requirements of the “National Basic Public Health Service Specification (Third Edition) [15]”.

**Fig. 3 Fig3:**
[figure not shown]
IoT-based hypertension surveillance system

### Sample size calculation

A formal power calculation was performed a priori using G*Power software (version 3.1.9.7) for the primary outcome: the between-group difference in blood pressure control rate.

The anticipated control rate in the control group (P₁) was conservatively estimated at 45%, informed by historical data from our health center and findings from literature on usual care in similar settings [16]. We hypothesized that the IoT-based intervention would yield a clinically meaningful absolute improvement of 10% points, raising the control rate in the intervention group (P₂) to 55%. This effect size is supported by a recent meta-analysis of mHealth interventions [16], which reported a significant absolute improvement yet considerable heterogeneity among studies.

Using a two-sided significance level (α) of 0.05 and a power (1-β) of 80%, the calculation indicated a minimum requirement of 350 participants per group (total *n* = 700). Accounting for an estimated 15% attrition rate, the sample size was adjusted to 412 per group (total *n* = 824).

However, considering that there are more than 80,000 hypertension patients in this region and approximately 20,000 hypertension patients who have signed contracts with family doctors in this community, in order to achieve better research results and based on the available research resources, it was finally decided to include 2,000 patients, with 1,000 patients in the intervention group and 1,000 patients in the control group. This larger sample size ensures robust power for the primary and all secondary outcomes, enables precise subgroup analyses, and provides high-quality, generalizable evidence essential for informing public health policy on chronic disease management.

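### The stated sample-size inputs require about 392 patients per group, not 350, and 462 after attrition, not 412; the planned 1,000 per group is unaffected

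*Protocol article*

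**What the plan says.** The Sample size calculation section describes a formal a priori calculation in G*Power 3.1.9.7 for "the between-group difference in blood pressure control rate". All the inputs are given:

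- Control group: "The anticipated control rate in the control group (P₁) was conservatively estimated at 45" per cent.
- Intervention group: a gain of 10 percentage points, "raising the control rate in the intervention group (P₂) to 55" per cent.
- Error rates: "Using a two-sided significance level (α) of 0.05" and "a power (1-β) of 80" per cent.

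The result is given as follows: "the calculation indicated a minimum requirement of 350 participants per group", or 700 in total. For 15% attrition, "the sample size was adjusted to 412 per group", or 824 in total. The section does not name the test chosen in the software. The Statistical analysis section plans a chi-square test for categorical variables.

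Enrolment is then fixed on other grounds, namely the number of contracted patients available and the research resources: 2,000 patients, "with 1,000 patients in the intervention group and 1,000 patients in the control group".

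**The concern.** Rates of 45% and 55% lie symmetrically about one half, where the binomial variance is largest. A 10-point difference there is known to need close to 400 patients per group at 80% power, so 350 looks too small to be a matter of rounding or choice of formula. The article prints every input together with an output that they do not seem to produce, so this is a stated figure that can be checked and not a detail left to a fuller document.

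At stake is the credibility of the power statement for the primary outcome. A reader who repeats the calculation will not reach 350. A reader who relies on it will believe that 350 analysable patients per group deliver 80% power, and will measure the margin of the larger enrolment from too low a base.

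**Working it through.** **Inputs, all from the Sample size calculation section.** p1 = 0.45, p2 = 0.55, difference d = 0.10, mean rate 0.50, two-sided alpha 0.05 (z = 1.960), power 80% (z = 0.8416), attrition 15%. Allocation is 1:1, as the equal group sizes imply.

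**Step 1. Try to reproduce 350.** Pooled-variance z-test, which is the counterpart of the chi-square test without continuity correction:

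n = [1.960 × √(2 × 0.5 × 0.5) + 0.8416 × √(0.45 × 0.55 + 0.55 × 0.45)]² / 0.10²

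= [1.960 × 0.7071 + 0.8416 × 0.7036]² / 0.01 = (1.3859 + 0.5921)² / 0.01 = 391.3, so **392 per group**, 784 in total.

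Other standard versions, same inputs, two-sided:

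| Method | n per group |
|---|---|
| Unpooled z: (1.960 + 0.8416)² × 0.495 / 0.01 = 388.5 | 389 |
| Arcsine: 2 × (1.960 + 0.8416)² / 0.2003² = 391.1 | 392 |
| Chi-square, w = 0.10: total 784.9, so 785 | about 393 |
| Pooled z with continuity correction: 411.02 | 412 |

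Dropping the two-sided requirement does not recover 350 either: one-sided versions at 80% power give 307 to 328 per group. A value near 350 appears only when a stated input is changed:

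- power of about 75%: 347
- a difference of about 10.6 points: 349
- one-sided alpha with 85% power: 359

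**Step 2. Power with 350 per group.**

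z = (0.10 × √350 − 1.3859) / 0.7036 = (1.8708 − 1.3859) / 0.7036 = 0.689, so power = **75.5%**. That is 4.5 points below the stated 80%.

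**Step 3. Attrition.** The article's own step reproduces: 350 / 0.85 = 411.8, so 412. From the corrected base, 392 / 0.85 = 461.2, so **462 per group**, 924 in total. The shortfall in the stated total is 924 − 824 = 100 patients, or 100 / 924 = about 11%.

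**Step 4. Effect on the planned trial, with independent patients.**

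- 1,000 per group: (0.10 × √1000 − 1.3859) / 0.7036 = 2.52, power 99.4%.
- 850 per group after 15% attrition: (0.10 × √850 − 1.3859) / 0.7036 = 2.17, power 98.5%.

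**The case against.** The strongest objection is that nothing depends on 350 or 412. The section moves from them to 2,000 on grounds of availability and resources, and its claim of robust power rests on the larger number. No enrolment target, analysis or decision threshold uses the smaller figures. This stands, and it limits the severity. It does not make 350 right.

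A reader might infer that the trial is underpowered. The documents do not support that: 1,000 per group is more than twice the corrected 462. A reader might also argue that the margin disappears once patients are treated as clustered within family doctor teams. That is a separate question. It would arise in the same way had the article printed 392, the article gives no intracluster correlation from which to size it, and correcting 350 would not settle it.

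Two possible rescues of the printed figures fail:

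- The continuity-corrected sample size happens to be 412. But the article obtains its 412 from 350 and 15% attrition. Had 412 been the base, the inflated figure would be 412 / 0.85 = 484.7, so 485.
- Controls are to be matched on age, sex and hypertension duration, so a paired calculation is conceivable. A McNemar approximation gives about 350 pairs if the discordant proportion is about 0.45, a within-pair correlation of about 0.11. The article states neither quantity and plans a chi-square test, so this does not reproduce 350 from the stated inputs.

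What the second point does show is that the test and the values entered in the software cannot be known from the article. An input may have been reported wrongly rather than the output. The correction should leave room for that.

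**Conclusion.** The point holds as an error in the reported calculation. On the stated inputs, the minimum is about 392 per group (784 in total) rather than 350 (700), and 462 per group (924 in total) after 15% attrition rather than 412 (824). With 350 analysable patients per group, power is about 75.5%. No standard two-sided method for two independent proportions gives less than 389.

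The result assumes equal groups, independent patients and an unpaired test, which agrees with the planned chi-square test. On the same assumptions, the planned enrolment keeps about 99% power, or 98.5% after attrition. The error therefore touches the published justification and not the enrolment target. Severity is moderate: a stated sample size is wrong as written, but the size of the trial does not depend on it.

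**What to change.** In the Sample size calculation section, do one of the following:

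1. Replace 350/700 with 392/784 and 412/824 with 462/924, and name the test as a two-sided comparison of two independent proportions, in line with the chi-square test in the Statistical analysis section.
2. If other inputs or another test were entered in G*Power, state them in full so that 350 can be reproduced, and correct whichever printed input differs.

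Keep the planned 2,000. The change costs a sentence or two. It adds no patients and leaves the analysis as it is. The stated minimum becomes somewhat larger, and the planned enrolment still exceeds it comfortably under independence.

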### Participants, selection criteria and recruitment

The study targets hypertensive patients managed under the family doctor contract service at Liyuan Community Health Center and its subordinate Community Health Station in Tongzhou District, Beijing. The intervention group (IG) will consist of 1,000 hypertensive patients randomly selected from five family doctor teams at Liyuan Community Health Center and subordinate Xiaogao Station where the IoT-based hypertension monitoring system is deployed. The control group (CG) will include another 1,000 hypertensive patients from other stations without the system, matched for baseline characteristics.

Participants must meet the following inclusion criteria to be enrolled in the study. First, they must be aged 35 years or older and have a confirmed diagnosis of primary hypertension as defined by the Chinese Hypertension Clinical Practice Guidelines [17], which requires systolic blood pressure ≥ 140 mmHg and/or diastolic blood pressure ≥ 90 mmHg measured on at least two separate occasions to ensure diagnostic accuracy. Second, they must be residents within the administrative jurisdiction of Liyuan Health Center and have signed a family doctor contract, which is a prerequisite for accessing hypertension management services under the National Basic Public Health Service Program [18]. This ensures that participants are eligible for the standardized care and monitoring provided by the health center’s healthcare teams. Third, participants must demonstrate the functional capacity to attend outpatient visits either independently or with minimal assistance, excluding those who are bedridden or require full-time care. This criterion is essential to ensure that participants can engage in regular blood pressure measurements, follow-up consultations, and health assessments as required by the study protocol, thereby facilitating the collection of reliable data on hypertension management outcomes.

Participants will be excluded if they meet any of the following criteria to ensure the safety and validity of the research results. First, individuals with a history of acute cardiovascular or cerebrovascular events, such as stroke, myocardial infarction, or aortic disease, occurring within the past 12 months are excluded, as these conditions may confound the assessment of hypertension management outcomes and require specialized clinical interventions that could interfere with the study’s standardized procedures. Second, participants with severe comorbidities, including heart failure, severe renal failure, or cancer, are ineligible, as their complex medical conditions may reduce their capacity to adhere to the study’s monitoring protocols and could lead to substantial variability in health-related outcomes. Third, individuals with uncontrolled psychiatric conditions (such as schizophrenia or severe depression with suicidal ideation) will be excluded, as these conditions may compromise study participation, data accuracy, or patient safety. Fourth, patients aged over 80 years or those with severe mobility impairment (defined as the inability to ambulate even with assistive devices) are excluded, as their limited physical capacity may hinder regular attendance and adherence to the study’s follow-up schedule. Finally, pregnant or lactating females are excluded due to the unique physiological changes and medication considerations during this period, which require specialized care outside the scope of the study’s focus on primary hypertension management in the general adult population. These exclusion criteria are designed to minimize confounding variables and ensure that the results reflect the true impact of the intelligent monitoring system on hypertension patients under routine primary care settings.

Eligible participants will be identified through Liyuan Health Center’s electronic health record (EHR) system, which maintains a registry of approximately 20,000 registered hypertension patients. The research team will use EHR data to pre-screen candidates, filtering for age, diagnosis, contract status, and exclusion criteria, after which random selection will be performed using a computer-generated random number table, stratified by age and sex to ensure demographic balance. Meanwhile, the control group (CG) will match to the intervention group (IG) on age, sex, and hypertension duration using EHR data to minimize baseline confounding.

### Study conduct

Eligible patients will be recruited via text messages or in-person during clinic appointments, explaining the study objectives, procedures, and voluntary nature of participation. Those interested will be contacted by research nurses for a telephone or in-person consultation to review the study details, including risks, benefits, and data confidentiality. Written informed consent will be obtained prior to enrollment. Upon consent, participants will complete a baseline assessment comprising: (1) demographics (age, sex, education); (2) clinical metrics: blood pressure (measured twice at rest, 5 min apart), BMI, fasting labs for lipids/glucose/renal/liver function, duration of hypertension, known comorbidities (e.g., diabetes, coronary artery disease); (3) functional assessment: mobility status (e.g., walking ability, use of assistive devices) and adherence to hypertension management (e.g., medication compliance, clinic visit frequency).

Following blood pressure measurement, the intervention group’s data will be automatically transmitted to the electronic health record system via IoT-enabled devices, where values are instantly integrated into statistical analyses and visualized on clinic display screens for real-time monitoring by both clinicians and patients. The system will trigger alerts for uncontrolled hypertension (systolic blood pressure is greater than 180 mmHg or diastolic blood pressure is greater than 110 mmHg [17]), enabling timely clinical decisions (medication adjustments/referrals). Participants will receive printed personalized reports with trend analyses and educational materials after each measurement. The control group will receive standard care via traditional health huts without IoT integration, with data manually recorded in electronic health records.

A three-month interval is deemed adequate for the initial follow-up, given the service intensity and participants’ functional capacities. Both groups will undergo quarterly follow-ups (three months, six months, nine months, one year) to collect the primary outcome (blood pressure control rate) and secondary outcomes (standardized management rate, measurement completion rate, referral rates for refractory hypertension, changes in biochemical indicators like lipids and fasting glucose), with data collected from IG’s real-time IoT measurements and CG’s traditional health hut’s records. If participants do not proceed with subsequent follow-ups, they will be contacted by phone and encouraged to continue their involvement.

At the conclusion of the one-year trial, questionnaire surveys and interviews with professionals will be carried out. Professional interviews will be conducted via focus groups at the trial’s end. The discussions will be structured around three key themes: (1) System usage experiences: Exploring practical aspects of the IoT-based hypertension surveillance system, including its integration into clinical workflows, data accuracy, and any adaptations made during deployment. (2) Implementation challenges and facilitators: Identifying organizational factors (e.g., resource allocation), technical factors (e.g., device connectivity), and patient-related factors (e.g., adherence behaviors) that influence system effectiveness. (3) Program theory refinement: Examining how the intervention’s components (real-time monitoring, alerts, patient engagement tools) interact to achieve outcomes, and proposing improvements to optimize hypertension management pathways. Sessions will include physicians, nurses, and administrators to capture diverse perspectives. Additionally, assistance is provided throughout the study to help complete the survey, particularly for individuals with visual impairments or other difficulties.

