## Methods

### Overall study design and setting

This study is a pragmatic quasi-experimental trial aimed at evaluating the effectiveness and feasibility of an IoT-based hypertension monitoring and management system in primary care settings. The overall study design is described in Fig. 1. The study compares outcomes between an intervention group (IG) using the IoT system and a control group (CG) receiving standard care. Quantitative data will assess clinical outcomes including blood pressure control rates, standardized management rates, and healthcare utilization, while qualitative methods will examine user experiences and implementation barriers through surveys and interviews with patients and healthcare providers (Fig. 2).

The study is carried out in Liyuan Health Center and its affiliated community health service stations in Tongzhou District, Beijing, P.R. China. The research area covers a large population of hypertension patients. It serves a population of approximately 250,000 people in urban and suburban regions, where the hypertension prevalence reaches as high as 33.3% [3]. The intervention is deployed across five family doctor teams in Liyuan Community Health Center and Xiaogao Community Health Station. These sites represent typical primary care institutions in Beijing’s urban expansion areas, serving mixed populations of long-term residents and recent migrants. The center utilizes Beijing’s municipal health information platform (B/S architecture) and has pre-existing health huts with basic measurement capabilities. The new IoT system integrates with these platforms through application program interfaces (APls) [13], enabling real-time data transmission from 6 intelligent monitors to electronic health records.

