During the clinical practice application stage, all research subjects are randomly selected from the currently managed patients. 1000 hypertension patients who have signed contracts with the family doctor teams of 5 teams in Liyuan Health Center and Xiaogao Community Health Service Station where the system is deployed are selected as the intervention group. These patients use the IoT-based hypertension supervision platform for blood pressure measurement, and their data is included in the new system for statistical analysis. Another 1000 hypertension patients who have signed contracts with the family doctor teams of other subordinate stations in Liyuan Health Center where the system is not deployed are selected as the control group. They only measure blood pressure in the health huts, and their data is not included in the new system for statistical analysis.

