### Outcomes and variables

The primary outcome of the trial is blood pressure control rate, which is the proportion of patients whose blood pressure is maintained within the target range. According to the National Basic Public Health Service Specification (Third Edition) [15], blood pressure should be controlled below 140/90 mmHg for individuals aged 35–65 years, and below 150/90 mmHg for those aged 65 years and above. Secondary outcomes: (1) standardized management rate: Calculated as the proportion of patients in the intervention and control groups who receive management in accordance with the National Basic Public Health Service Specification (Third Edition) [15], to evaluate the impact of the system on the standardization of hypertension management; (2) blood pressure measurement completion rate: The number of blood pressure measurements completed per patient compared to the expected quarterly measurements; (3) Referral rates: The number of patients referred to higher-level hospitals due to refractory or secondary hypertension, and the proportion of referred patients whose blood pressure stabilizes upon return; (4) Biochemical indicators: Changes in lipid profiles and other relevant biomarkers.

In addition, exploratory outcomes are economic evaluation(cost-effectiveness: analysis of system deployment costs versus improvements in hypertension control and reduced referrals; performance incentives: correlation between system-generated data and family doctor contract fulfillment metrics for incentive allocation), patient satisfaction (the subjective experiences and perceived effects), implementation barriers (engage professionals in focus groups and interviews to examine implementation barriers and improvement opportunities from the service providers’ perspective).

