### Statistical analysis

Statistical analysis will be performed using SPSS 27.0. Normality of continuous variables (e.g., blood pressure values, biochemical indicators) will be assessed using Shapiro-Wilk tests. Normally distributed data will be presented as mean ± standard deviation (x̄ ± s) and analyzed with independent t-tests for between-group comparisons (intervention vs. control) and paired t-tests for within-group changes (baseline vs. follow-up). Non-normally distributed data will be reported as median (interquartile range) and analyzed using Mann-Whitney U test. Categorical variables will be expressed as counts (%) and compared via the chi-square test. A two-sided p-value < 0.05 will indicate statistical significance.

Intention-to-treat analysis will be prioritized [19], with multiple imputation for missing data. Subgroup analyses will be performed for age, hypertension severity, and comorbidity status. In addition, insights on implementation barriers and improvement strategies derived from focus groups and interviews with healthcare professionals will be systematically analyzed using thematic analysis.

The economic evaluation is integrated into the quasi-experimental trial design, comparing the IoT-based hypertension surveillance system (intervention group, IG) with standard care (control group, CG). Costs and outcomes are assessed over a 12-month period to determine incremental cost-effectiveness. The analytical method is Incremental Cost-Effectiveness Ratio (ICER) [20], which is calculated using the following method. Where: ΔC = Change in mean costs (intervention vs. control). ΔE = Change in mean effectiveness (e.g., blood pressure control rate). Bootstrap simulation with 1,000 replications will be conducted to generate ICER distributions, plotted graphically on cost-effectiveness planes.$$\:ICER=\frac{\left({\Delta\:}{C}_{IG}-{\Delta\:}{C}_{CG}\right)}{\left({\Delta\:}{E}_{IG}-{\Delta\:}{E}_{CG}\right)}$$

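### Intervention-group blood pressure follow-up is tied to the IoT machines, with no rule for readings taken off the system, which weakens the intention-to-treat estimate

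*Protocol article*

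**What the plan says.** Under Study conduct, the protocol article sets the schedule: "Both groups will undergo quarterly follow-ups (three months, six months, nine months, one year) to collect the primary outcome" and the secondary outcomes, "with data collected from IG’s real-time IoT measurements and CG’s traditional health hut’s records". For the intervention group, the section on overall design and setting gives the same route: "These patients use the IoT-based hypertension supervision platform for blood pressure measurement, and their data is included in the new system for statistical analysis". For patients who lapse, the only step given is this: "If participants do not proceed with subsequent follow-ups, they will be contacted by phone and encouraged to continue their involvement". No other way of obtaining a blood pressure is named.

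The Statistical analysis section states: "Intention-to-treat analysis will be prioritized [19], with multiple imputation for missing data". It does not describe the imputation model.

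Other routes to a reading exist. The system consists of six machines in the general practice clinics of two sites (Study intervention), and the center "has pre-existing health huts with basic measurement capabilities". The Discussion concedes that data quality may differ between the two sources. It does not discuss who has a value at all.

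**The concern.** The point is not whether two devices read differently. It is whether a patient has an outcome. An intention-to-treat estimate needs the outcome of every patient in the assigned group, including those who no longer use the system. If the intervention group's blood pressures are drawn from the IoT system, a patient measured elsewhere has no value in the named source even when a valid reading exists. That patient would be handed to the imputation model, and the intervention control rate would move toward the rate among patients who kept using the machines.

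The loss may well be informative. Under Study intervention, each month's team figures are reviewed and published, and doctors are pressed to send patients who pull the control rate down to hospitals at a higher level. Readings taken while such patients are away are not IoT readings. The article describes no matching step for controls. If the patients measured elsewhere are less well controlled, the bias favours the intervention.

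The measurement completion rate is exposed too. It is defined as "The number of blood pressure measurements completed per patient compared to the expected quarterly measurements", so off-system readings in the intervention group would go uncounted.

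**Working it through.** **1. Inputs from the article (Sample size calculation).** Anticipated control rates are 45% (control) and 55% (intervention), a planned difference of 55 − 45 = 10 points. Attrition is 15%, and the article's inflation step reproduces: 350 / (1 − 0.15) = 411.8, rounded up to 412. The article gives no figure for patients measured off the system, so there is no stated value to reproduce on this point.

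**2. Inputs that are assumptions.** Let *s* be the share of intervention patients measured only off the system, *pc* the control rate in continuing users and *ps* the rate in those measured elsewhere. Take *pc* = 55%. The 15% is borrowed for *s* only as a convenient size: it is overall attrition, a different quantity.

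**3. Formula.** The true intervention rate is (1 − *s*) × *pc* + *s* × *ps*. If imputation gives the off-system patients the continuing users' rate, the reported rate is *pc*. The bias is therefore *s* × (*pc* − *ps*).

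**4. Results, in percentage points.**

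| *s* | gap 0 | gap 5 | gap 10 | gap 20 |
|---|---|---|---|---|
| 5% | 0 | 0.25 | 0.5 | 1.0 |
| 15% | 0 | 0.75 | 1.5 | 3.0 |
| 25% | 0 | 1.25 | 2.5 | 5.0 |

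Worked cell: *s* = 15%, gap 20, so *ps* = 35%. The true rate is 0.85 × 55 + 0.15 × 35 = 52.0%, and the bias is 55 − 52 = 3.0 points. A true difference of 52 − 45 = 7 points would be reported as 10.

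**5. Effect on the test when the intervention does nothing.** Set the true rate to 45% in both groups, *s* = 15%, 1,000 × 0.85 = 850 observed per group, and control losses unrelated to outcome.

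- Gap 10: the reported intervention rate is 46.5%, the standard error is √[(0.465 × 0.535 + 0.45 × 0.55) / 850] = 0.0242, and bias / SE = 0.62. The two-sided type I error is about 0.095 instead of 0.05.
- Gap 20: the reported rate is 48.0% and bias / SE = 1.24. The type I error is about 0.24.

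**6. Sample size does not help.** Power for 45% versus 55% is about 99.4% with 1,000 per group and 98.5% with 850. Enlarging the trial narrows the interval around a biased value.

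**The case against.** The sentence under Study conduct can be read as a loose summary. It covers laboratory and referral outcomes as well, which no blood pressure machine can supply, and it never says that other readings are discarded. The Study intervention section adds: "These devices are connected to the health hut and the residents’ personal health records, enabling real-time data transmission and analysis". Intervention data also go to the electronic health record. The machines stand in clinics, so a patient who attends a deployed clinic can be measured on them, and one who stops attending is lost much as a control who stops visiting the hut is lost. The imputation model is commonly left to the analysis plan, and the baseline data (blood pressure, medication compliance, visit frequency) could inform it.

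Much of this stands, and it rules out several stronger readings that a reader might infer:

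- That *all* intervention outcomes come only from the IoT system. Exclusivity is an inference and cannot hold for laboratory and referral outcomes, so the point is confined to blood pressure outcomes.
- That missing patients will be imputed from continuing users. No model is stated.
- That intention-to-treat is undone. Patients stay in their assigned group.
- That only one group is affected. Controls can lose data too; what differs is the source and its tie to the intervention.
- That control patients' readings on IoT machines are dropped. Controls come from stations without the system, and no such use is described.

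What does not fall is the core. The links to hut and record show that off-system readings may be retrievable, but nothing makes them an outcome source. No choice of imputation model justifies replacing a value that exists.

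**Conclusion.** The point holds for blood pressure outcomes, including the primary. As written, the availability of an intervention patient's outcome depends on use of the intervention, there is no provision for readings taken elsewhere, and the intention-to-treat estimate is weakened.

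The size cannot be determined from the document. The 1.5 to 3.0 points (15% share, gap of 10 to 20 points) illustrate the scale against a planned 10; they are neither an estimate nor an upper bound. They rest on an assumed share, an assumed gap, and imputation that returns the continuing users' rate. Imputation using earlier readings would reduce the bias, no gap would remove it, and better control among off-system patients would reverse it. Patients who leave with no reading anywhere are a separate missing-data problem that better extraction does not solve.

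**What to change.** State in the protocol that each quarterly blood pressure outcome is taken, for every enrolled patient and by assigned group, from any reading in the electronic health record within the window (IoT machine, health hut, clinic or station), whether or not the patient still uses the assigned system. Record the date and reason for stopping the system as an event distinct from leaving the study. Restrict multiple imputation to patients with no reading from any source in the window. Apply the same rule to the measurement completion rate. If off-system readings are already accepted, the sentence under Study conduct should say so.

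The cost is small. IoT readings are transmitted to the electronic health record, control readings are entered there by hand, and the record already serves for screening. Two limits remain. Intervention-group readings become less uniform, so the source of each should be recorded and a sensitivity analysis by source run. The rule also recovers only readings that reach the record: the article does not say whether those taken at a higher-level hospital do, and this should be established.
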